## Methods: data collection, management and analysis

### Data collection methods

Data will be collected for all workers at baseline (week 1) and follow up (week 12). Data from intervention workers’ planning tools will be collected every day from week 3 to 12. Records of participation rates (i.e., in educational, and implementation team meetings, cf. Table 1), and costs related to the intervention (e.g., staff time and consultant time) will be collected throughout the intervention period. All sensitive personally identifiable information will be collected at the workplace by the researchers. The information will then be transported back to the research center and will be uploaded on a secure drive, which is accessible only to researchers physically present at the center. Finally, when all information has been collected, one single file for each participant will be stored in a secure place. These files will remain stored for a period of 3 years after completion of the study. Once the dataset is complete, the information uploaded to the secure drive will be anonymized by a data manager.

### Participant characteristics and anthropometric measurements.

We will collect information about sociodemographic factors including age, gender, ethnicity, length of service, job title, and weekly work hours. Further, we will collect information about smoking and alcohol consumption [41]. We will measure height (Seca 213; Seca GmbH, Hamburg, Germany), weight (BC-418 MA body composition analyzer; Tanita, Tokyo, Japan), and calculate the body mass index (body weight [kg]/(body height squared [m2])). In addition, we will determine fat percentage (DC-430 SMA body composition analyzer; Tanita, Tokyo, Japan) and resting blood pressure (Omron M3 or Omron M6 Comfort; Omron Corporation, Kyoto, Japan) using standardized protocols.

### Physical behaviors

The protocol for measuring physical behaviors will be similar to that used in previous studies [16, 19, 42]. An AX3 accelerometer (3-Axis Logging Accelerometer; Axivity Ltd., Newcastle upon Tyne, UK) will be mounted using adhesive tape (Hair-Set double-sided adhesive tape; 3 M Company, Maplewood, MN, USA) on the worker’s right thigh at the most muscular part of the quadriceps femoris, midway on the line between the anterior inferior iliac spine and the top of the patella. Workers will be asked to wear the accelerometer around the clock for five consecutive days at baseline and follow up, and will be instructed on how to change the adhesive tape if necessary. At the end of day five, the accelerometer will be returned to the research team. Data will be downloaded using the manufacturer’s software (OMGUI, Configuration and Analysis Tool). A workday will be excluded from further analysis if accelerometer recordings are available for less than 4 h. Periods > 60 min without movement will be regarded as non-wear time or sleep.

Physical behaviors will be exhaustively classified using the Acti4 software [42] into time spent sitting or lying (termed sitting below), standing (consisting of time spent standing still, or standing with slight movement), and active (consisting of time spent walking, running, stair climbing or cycling).

During all measurement days, the workers will note in a diary at what time they: 1) woke up, 2) arrived at work, 3) left work, 4) went to sleep, and 5) if the accelerometer was detached at any time during data collection. On the basis of the diaries, the continuous timeline of physical behavior data will be partitioned into periods of, 1) work, 2) leisure time awake, and 3) time in bed.

### Planning tool

All workers in the intervention group will receive an e-mail immediately after baseline measurements with a unique link to an online folder containing the Excel planning tool. There will be a planning tool sheet every workday for the entire 10 weeks of the intervention (i.e., week 3 to 12, Fig. 3). Data will be automatically stored on an online drive (Microsoft, One Drive, 2021). Eventual data containing information about the four key variables evaluating fidelity will be saved on the secure drive.

### Questionnaires

The questionnaires consist of standard validated questions, as well as questions to describe the intervention process. At baseline and follow up we will collect information about musculoskeletal health [43], general health [44], need for recovery [45], self-assessed physical fitness [46], sickness absence, psychosocial work environment [47] and productivity [48–50]. Questionnaires using a numerical scale from 0–10 will be send at the end of the workday, for each of the first five days and the last five days of the intervention on; 1) pain, 2) fatigue and 3) energy [43]. Furthermore, customary questions will be used to collect information about participants’ use of medication and healthcare services.

### Quality of program delivery

Specific questions to evaluate the fidelity towards the intervention program will be formulated to reflect program quality, and motivation towards the intervention. These will be sent out to the local workplace group and course leaders using text messages after completion of all the training and implementation meetings. Furthermore, notes and records from meetings with the local workplace group will be used to assess fidelity regarding the implementation of the intervention.

### Costs

Costs of conducting the intervention activities will be collected. Costs include resources used by the organization to implement the intervention, and resources used by the researchers to deliver the intervention. Implementation costs for the organization will include staff time used by workers, work environment representatives, health & safety advisors and managers participating in training and implementation meetings. Time used by staff for other activities related to implementing the intervention will also be included. Costs will be estimated on basis of the average gross salaries of staff, including overhead. Costs of delivering the intervention for researchers will include the time used for preparing and conducting the training and implementation meetings, and any additional planning and meeting related to implementation of the intervention. Costs for researchers will be estimated based on their hourly fee, including overhead. Finally, costs related to workers’ productivity, sickness absence and consumption of medicine and health services (e.g., visits to a general practitioner or a physical therapist) will be collected at baseline and follow up.

### Statistical methods

Primary outcome will be assessed as the difference between intervention and control groups in change in low back pain following the 12 weeks intervention. We will use both intention-to-treat effect estimates and per-protocol effect estimates to assess the effectiveness of the intervention, as recommended when evaluating trials conducted in real life settings [51]. The per-protocol criteria is defined as work teams (clusters) who completes ≥ 60% of the available planning tools. Based on the distribution of data, parametric or non-parametric test will be performed.

The secondary outcomes include data of different types, i.e. categorical, continuous and compositional data. For all data types, descriptive statistics relevant to the variable will be applied. The statistical analysis used to assess differences between intervention and control groups will also be adapted to the type and distribution of the data. Specifically, changes in the physical behavior composition (i.e. sitting, standing, and active behavior), will be analyzed using CoDA metrics.

A detailed analysis plan describing comparison and test of changes in the intervention and control groups will be completed before initiating the analysis and will be available upon reasonable request.

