### Outcomes

#### Primary outcome measure

The primary outcome measure for the trial will be the difference between intervention and control groups in the change of low back pain intensity from baseline to follow up (12 weeks). We chose low back pain as an overall representation for musculoskeletal health (Fig. 2.), since it has a pronounced influence on both work ability [9], sick leave [10], and since it occurs in many pain patterns [35]. Pain intensity will be measured repeatedly on a numeric scale (NRS, 0–10). A question will be sent to the participants in a text message at the end of the workday for five consecutive workdays at baseline (week 1) and five consecutive workdays at follow up (week 12), asking them to rate their low back pain intensity.

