### Sample size

Previously, we have experienced a participation rate among eligible industrial workers of 84%, followed by a response rate of 87% of those participating [37]. At present, management in the participating organization has estimated that 110 workers will be eligible for the present study. Based on our previous experience, we assume that 80% will be willing to participate in our study (i.e., 88 workers) and that 20% will be lost to follow up. Thus, assuming that 70 participants, organized in clusters with an average size of *n* = 4 (range *n* = 2 to *n* = 7), will complete the study, we may estimate the detectable effect size in a cluster randomized controlled design as follows:

In our previous feasibility study among industrial workers [16], we found that low back pain intensity was, on average, 3.7 points (on a 0–10 scale) with a total variance between workers of 10.6. This total variance will be reduced with repeated measurements over days in each subject. Within-subject (between-days) variance was 1.6, or 15% of the total variance (between-subject and within-subject) of low back pain. If we repeat measurements for 5 days, the within-subject variance will be reduced to 0.3, resulting in an estimated total variance of 9.3. Based on this, we can – given the sample size stated above, i.e. *n* = 70 – expect to be able to detect a 1.5 point difference between groups in low back pain intensity, at a significance level of 0.05, a power of 0.80, and a cluster size of 4 (the average size).

The effect on low back pain intensity from redesigning physical behaviors at work is unknown. In our feasibility study, we found a mean difference of 1.1 in low back pain intensity between usual and redesigned workdays [16]. However, we cannot draw any firm conclusion about the expected effect size from that study due to the difference in study design, the limited sample size (*n* = 14) and, hence, the large uncertainty in data. Nevertheless, reducing low back pain intensity by 1.5 is likely to be a meaningful clinical and work-related change [38]. Therefore, we find it meaningful to conduct the present study despite its uncertainties.

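### The primary effect is defined as a difference in change with no stated baseline adjustment; followed as written it leads to a less precise test of change scores

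*Protocol article*

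**What the plan says.** The Primary outcome measure section defines the effect as "the difference between intervention and control groups in the change of low back pain intensity from baseline to follow up (12 weeks"). Low back pain is rated 0–10 by text message on five workdays in week 1 and five in week 12, so every worker who responds has a baseline five-day mean.

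The Statistical methods section repeats the definition: "Primary outcome will be assessed as the difference between intervention and control groups in change in low back pain following the 12 weeks intervention". On method it adds only this: "Based on the distribution of data, parametric or non-parametric test will be performed". The rest is deferred: "A detailed analysis plan describing comparison and test of changes in the intervention and control groups will be completed before initiating the analysis". No model and no covariate is named for the primary outcome. Neither section calls the comparison raw or unadjusted, and neither rules out a covariate.

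**The concern.** A difference in change, a choice between parametric and non-parametric tests, and a deferred plan to test changes all point the same way: compute each worker's change and compare the two groups. A standard rank test of change has no place for a covariate.

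That route uses the baseline inefficiently. Subtracting it assumes that a worker who starts one point higher would, without treatment, finish one point higher. If the 12-week correlation is below 1, regression to the mean makes the expected gap at follow-up smaller than one point. Subtraction then over-corrects, and the arm that happens to start with more pain appears to improve more. Adjusting for baseline as a covariate estimates the same treatment effect with less variance. With about 35 completers per arm, the precision is worth having.

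**Working it through.** **Inputs from the Sample size section**
- Completers: "assuming that 70 participants, organized in clusters with an average size of" four, so 35 per arm at 1:1 allocation.
- Total variance 10.6, of which 1.6 is between days. For a five-day mean: 10.6 − 1.6 + 1.6/5 = 9.32, which agrees with the stated 9.3. This is the variance at a single time point, not of a change.
- Significance level 0.05, taken here as two-sided, and power 0.80: multiplier 1.960 + 0.842 = 2.802.

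**Assumptions.** The protocol gives no 12-week correlation r, so a range is shown. Variances are taken as equal at both times. Clustering is left out because no intracluster correlation (ICC) is given.

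**The plan's own figure.** The section says the trial can "expect to be able to detect a 1.5 point difference between groups in low back pain intensity, at a significance level of 0.05". From its inputs, 2.802 × √(2 × 9.3/35) = 2.04, not 1.5. That is a separate issue and nothing below depends on it.

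**Variance per worker**
- Change score: 9.3 + 9.3 − 2r × 9.3 = 2(1−r) × 9.3.
- Baseline-adjusted: (1−r²) × 9.3.
- Ratio, adjusted to change: (1−r²)/[2(1−r)] = (1+r)/2, which is below 1 for every r below 1.

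**Detectable difference** = 2.802 × √(2 × variance/35)

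| Assumed r | Variance: change / adjusted | Detectable difference: change / adjusted | Power for 1.5 points: change / adjusted | Variance saved |
|---|---|---|---|---|
| 0.5 | 9.30 / 6.98 | 2.04 / 1.77 | 54% / 66% | 25% |
| 0.7 | 5.58 / 4.74 | 1.58 / 1.46 | 76% / 82% | 15% |
| 0.9 | 1.86 / 1.77 | 0.91 / 0.89 | 99.6% / 99.7% | 5% |

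If r were below 0.5, the change score would be noisier than ignoring baseline: at r = 0.3 it detects 2.42 points, against 2.04 from follow-up alone and 1.95 with adjustment. An assumed ICC of 0.05 with teams of four gives a design effect of 1 + 3 × 0.05 = 1.15. That raises every detectable difference by about 7% (√1.15 = 1.07) and leaves the comparison between the methods unchanged.

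**Chance baseline imbalance.** The standard error of the difference in baseline means is √(2 × 9.3/35) = 0.73 points. A change score keeps (1−r) of an imbalance. For an imbalance of one standard error, the estimate shifts by:
- 0.5 × 0.73 = 0.36 points at r = 0.5
- 0.3 × 0.73 = 0.22 points at r = 0.7
- 0.1 × 0.73 = 0.07 points at r = 0.9

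**The case against.** The best reply is that the protocol fixes an effect measure, not an analysis. A model of change with baseline as a covariate gives exactly the treatment effect of a baseline-adjusted model of week-12 pain, and it fits the quoted sentences. Covariates are also what a protocol article commonly leaves to its analysis plan. This stands in part. A reader might infer that the protocol has chosen raw change scores over adjustment, and the text does not support that. The absence of a named covariate is not in itself a fault. What remains is that the wording the article does commit to, including its description of the deferred plan, leads to a test of changes.

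The size of the gain is also open to challenge. The protocol gives no r, and at 0.9 the saving is slight. The day-to-day figures imply a short-term reliability of 9.0/9.32 = 0.97 for a five-day mean, but that does not establish the correlation over 12 weeks.

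Three stronger readings should be resisted:
- The 95% range of a chance baseline difference (1.96 × 0.73 = ±1.4 points) looks alarming beside the 1.5-point target, but only (1−r) of it reaches the estimate: about ±0.7 at r = 0.5 and ±0.4 at r = 0.7.
- Chance imbalance costs precision. It does not bias the change score over repeated randomisations.
- Baseline adjustment is not the only precision gain that needs no additional worker. Adjusting for site, by which randomisation is stratified, may also help.

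**Conclusion.** The point holds as an improvement to make, not as an error in what the protocol states. The wording leads to a comparison of change scores, and a baseline-adjusted estimate of the same effect is more precise for every r below 1. Under equal variances, 35 per arm and no clustering, the variance saving is 25%, 15% and 5% at assumed correlations of 0.5, 0.7 and 0.9. The protocol cannot say where in that range the trial lies.

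One limit applies to either analysis. The section on assignment of interventions has workers told their group after the physical assessment, and the Questionnaires section places the first daily ratings in the first five days of the intervention. Baseline pain may therefore be reported with allocation known, in which case a difference between arms need not be due to chance. Neither subtraction nor adjustment cures that.

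**What to change.** State in the analysis plan, before outcome data are examined, that the primary estimate is the difference between arms in week-12 low back pain adjusted for the worker's baseline five-day mean (equivalently, change with baseline as a covariate), from a model that accounts for team clustering and site. Report mean change by arm descriptively. Do the same for the daily fatigue, energy and exertion ratings.

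A constrained longitudinal model would also keep workers who have baseline but no follow-up data. It assumes equal baseline means in the two arms, however, and ratings given with allocation known would undermine that assumption. It should not be adopted without settling when baseline ratings are collected relative to disclosure.

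The cost is one sentence, with no new data and no additional workers.

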## Discussion

This protocol describes a 12-weeks Goldilocks Work intervention among industrial workers. The primary hypothesis is that implementing a ‘just right’ physical behavior among workers will lead to improved musculoskeletal health.

### Strengths and limitations

The 4-step procedure and participatory approach that guided the development of the program logic and the intervention is a strength of this protocol. The cluster randomized controlled design with randomization performed at each production site is a strength because it reduces potential bias. The planning tool adapted to the workers’ context is a strength because it offers an easy-to-use and practical approach for their own planning of work tasks to change behavior. The approach of feeding back information from the planning tool to the workers is also a strength that can improve the likelihood that workers’ behavior is changed [34]. Furthermore, the information collected about the implementation process is a strength because it may inform details about who did what when, and explain why things turned out as they did.

A limitation is that participants are not blinded to their allocation; this can increase the risk of selection bias. However, workers will not receive knowledge of their allocation until after they completed their eligibility screen and health check. Another limitation is the short duration of the study (i.e., 12 weeks), since it may take longer to effectively implement changes in physical behavior and thus effectively improve musculoskeletal health. However, even if the intervention is not effective, the workers and the workplace will gain valuable knowledge about their work context, the current physical behavior, and which changes that may improve workers’ health on the long term.

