### Trial design

The Goldilocks Work intervention will use two parallel groups, with an allocation ratio of 1:1. Work teams consisting of 1–7 workers, as already organized at the workplace, will be randomly allocated to either an ‘intervention group’ receiving the intervention, or a ‘control group’ performing work as usual.

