### Participant timeline

The schedule of enrolment, intervention and assessment is presented in Table 2. Together with the organization, we found suitable and interested production sites. Within these participating production sites we will randomize clusters (i.e., teams of workers), to either intervention or control. Subsequently, workers within each cluster will be invited to participate, assessed for eligibility, and followed during the intervention period. Non-participants, loss to follow up, the extent of lost data and the amount of data used for final analysis will be reported.

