## Methods: assignment of interventions

First, workers will be asked by a researcher if they wish to participate in the study. Workers agreeing will then sign an informed consent, and workers declining will be counted as non-participants. After signing the informed consent, workers will complete a physical assessment and following that, they will be verbally informed about their group allocation. This is necessary because we need to plan training activities with the work teams and the local workplace group. Additionally, we need to prepare the planning tool to comply with the specific work tasks of the work teams allocated to the intervention.

Due to the nature of the intervention, it is not possible to blind the workers to their allocation. Additionally, during enrolment, blinding of the assessors is not possible. However, the main outcome, musculoskeletal health, is measured through questionnaires sent out via text messages, and thus, is not affected by our inability to blind the assessors during enrolment. Furthermore, all secondary outcomes are collected with either wearable sensors or questionnaires, and will not be biased by lack of assessor blinding.

Clusters (i.e. teams) will be randomly allocated to the intervention and control groups in a 1:1 ratio. The teams will be allocated using SAS version 9.4 and the function RANUNI, which returns a number generated from a uniform distribution on the interval (0, 1) [39]. The randomization process will be performed separately for each production site, i.e., the randomization will be stratified. Clusters within a production site receiving values in the lower half of numbers drawn at that site will be assigned to the intervention, and clusters with values in the upper half will be controls. A data manager not otherwise involved in conducting the intervention will generate the allocation sequence for each production site.

Intervention and control workers will be present at all included production sites. This allocation procedure was chosen to reduce the risk of bias due to changes in contextual factors (e.g., change in management, structural changes, or supply chain challenges) during the intervention period, which have been shown to occur quite often [40]. Furthermore, it may also reduce potential bias from contextual differences that may exist between sites, such as differences in work tasks, restrictions in production complicating work planning, or how machines are operated.

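### The safeguard against selection bias is worded for the single worker, but teams are allocated, and nothing requires a whole team to be enrolled before any member is told its arm

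*Protocol article*

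**What the plan says.** All references are to the protocol article.

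- **Unit of allocation** (Trial design): "Work teams consisting of 1–7 workers, as already organized at the workplace, will be randomly allocated".
- **Order of randomisation and recruitment** (Participant timeline): "Within these participating production sites we will randomize clusters (i.e., teams of workers), to either intervention or control". The next sentence reads: "Subsequently, workers within each cluster will be invited to participate, assessed for eligibility, and followed during the intervention period". The arm therefore exists before anyone in the team is approached.
- **Order within enrolment** (Methods: assignment of interventions): workers are asked, and those who agree sign consent. Then "workers will complete a physical assessment and following that, they will be verbally informed about their group allocation". The reason given is practical: "This is necessary because we need to plan training activities with the work teams and the local workplace group". The same section adds: "Additionally, during enrolment, blinding of the assessors is not possible".
- **The risk and the answer to it** (Strengths and limitations): "A limitation is that participants are not blinded to their allocation; this can increase the risk of selection bias". The only protection then offered is "However, workers will not receive knowledge of their allocation until after they completed their eligibility screen and health check".

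**The concern.** A rule that withholds the arm until a worker has been screened and assessed suits individual randomisation, where one person's allocation says nothing certain about a colleague's. Here the team shares one allocation. Once any member knows it, it is known for every teammate, including those who have not yet been asked to take part.

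At stake is who joins. If workers can decide with knowledge of their arm, participation can depend on arm and on pain together. For example, workers with back pain might be readier to join in intervention teams than in control teams. The enrolled groups would then differ in ways that randomisation of teams does not prevent, and an intention-to-treat analysis of those enrolled does not undo it. The primary outcome is self-reported and unblinded, and about 70 completers are expected, so the trial has little room for this.

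**Working it through.** No figure in the plan bears directly on this point. The check is a comparison of the stated order of events, followed by a count.

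**Order of events**

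1. Teams are randomised within site (Participant timeline).
2. Workers in each team are invited and screened (Participant timeline).
3. Workers consent, or are counted as non-participants (Methods: assignment of interventions).
4. Consenting workers are physically assessed and afterwards told the arm (same section).

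Take two members of one team, A and B. The text requires that A decides before A is told, and that B decides before B is told. Because the arm is common to both, B's decision is certain to be uninformed only if B decides before *either* of them is told. No section shown states that second condition. The Planning tool section does not supply it either: intervention workers are e-mailed their link once baseline measurements are done, again with no reference to the rest of the team.

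**How many workers could be affected**

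Inputs: 110 eligible workers (Sample size), 28 teams expected (Abstract, Methods), teams of 1–7 (Trial design).

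Suppose a team has m eligible members who are told one by one. The first is sure to decide uninformed, and up to m − 1 could be informed, a share of (m − 1)/m:

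| m | Largest share informed |
|---|---|
| 1 | 0/1 = 0% |
| 2 | 1/2 = 50% |
| 4 | 3/4 = 75% |
| 7 | 6/7 = 86% |

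Over the whole trial:

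- Average team: 110/28 = 3.93 eligible workers.
- Sum of (m − 1) over the 28 teams: 110 − 28 = 82, however the 110 are spread across the teams.
- Largest share informed: 82/110 = 74.5%, about 75%.
- Sure to be uninformed: 28/110 = 25.5%, about 25%.

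If each team is told only after its last member has decided and been assessed, the count by this route is 0 of 110.

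The figure of 82 is a ceiling. It assumes strictly sequential disclosure, that the first member approached in every team consents and is told, and that the news always reaches the others. Decliners are not described as being told, so a team whose first member declines has more than one member deciding uninformed.

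**The case against.** Most of the case on the other side limits the point, and most of those limits stand.

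- **Individual, immediate disclosure is not stated.** A reader might infer that each worker is told alone, directly after his or her own check. The text is in the plural and gives only an order. It fits equally well with telling a team together, and the reason given for disclosure concerns teams. This stands: the documents permit staggered disclosure but do not describe it.
- **The safeguard does something.** A reader might conclude that there is no protection at all. That goes too far. The rule stops researchers telling a worker before that worker's own consent and assessment. It fully covers one-person teams and the first member told, and it would cover everyone if teams are told together.
- **The protocol does not claim that the risk is gone.** It lists selection bias as a limitation and promises to report non-participants. This stands, but that reporting is not tied to arm or to the time of disclosure.
- **A condensed article may omit the detail.** The enrolment schedule (Table 2) and the timeline (Fig. 3) are not shown and may settle it. This stands in part. The Discussion nevertheless argues that the risk is mitigated, and that argument needs the team-level condition to be correct.
- **The share informed is not a bias in pain points.** A reader might turn the 75% into some fraction of the 1.5-point detectable difference. The documents give no joining rates by arm and pain. The trial also compares change from baseline, so a baseline gap is not a bias of the same size. If workers with more and less pain change alike apart from treatment, a baseline gap adds no bias to the change.

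**Conclusion.** The point holds as a gap in the stated safeguard. Allocation is by team and precedes invitation, while the protection is framed per worker. Nothing shown prevents one member from being told while teammates have yet to decide, so the safeguard is not secured at team level.

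The exposure lies between 0% (disclosure waits for the whole team) and at most about 75%, or 82 of 110 workers (disclosure one by one, with full leakage). The documents do not say where in that range the trial sits. The size of any bias in the change in low back pain cannot be derived from them, and no figure in pain points should be attached. The change is a cheap improvement that should be made. If teams were in fact told together, one added sentence closes the matter.

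**What to change.** 1. In Methods: assignment of interventions, state that allocation is disclosed once per team, and only after its last eligible member has either declined or has consented and completed the physical assessment.
2. Log each worker's consent date and each team's disclosure date, so that anyone enrolled after disclosure can be flagged and examined in a sensitivity analysis.
3. Report participation and baseline pain by arm, alongside the promised account of non-participants.
4. In Strengths and limitations, limit the claimed protection to that basis.
5. Study setting says that implementation is already under way. For teams already enrolled, reconstruct the consent and disclosure dates as far as records allow, and correct the wording in Strengths and limitations.

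**Cost.** Some wording, two logged dates, and a short delay in telling the earliest-assessed workers and in planning training with them. The length of the delay depends on how long a team takes to enrol, which the article does not give. Planning-tool sheets run only from week 3, which leaves some room, and preparing the tool requires the research team, not the workers, to know the allocation.
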